#### Secondary outcomes

Performance accuracy (sensitivity, specificity, NPV and PPV) in identifying *clinically important CSI* (table 3) of (1) the PECARN risk criteria, (2) the two adult-derived CDRs (NEXUS and CCR), (3) current CSI management practice and (4) any newly developed exploratory SONIC CDR.Performance accuracy (sensitivity, specificity, NPV and PPV) in identifying CSI as defined by existing CDRs or risk criteria of (1) the PECARN risk criteria, (2) the two adult-derived CDRs (NEXUS and CCR), (3) current CSI management practice and (4) any newly developed exploratory SONIC CDR.Performance accuracy (sensitivity, specificity, NPV, PPV) in identifying patients with *study-defined CSI* with any newly developed exploratory SONIC CDR.Rates of study defined CSI; imaging-confirmed CSI; clinically important CSI; CSI-related neurological abnormalityRate of surgical intervention of the cervical spine for CSIDetermination of missed CSI rates, if any, with different cervical spine imaging modalities (XR vs CT vs MRI)Methods of, duration of and adverse events associated with cervical spine immobilisationCost effectiveness of CDRs and different imaging modalities compared with usual clinical care.Epidemiology of CSI in participating countries.

### Definitions

See table 3.

### Patient recruitment, study procedures and data collection (flow chart, data collected)

All patients presenting to participating EDs will be screened for eligibility. Treating clinicians will enrol eligible patients. Identification of potentially eligible and missed eligible patients will be undertaken by the research team in each participating centre through a review of ED attendance records. Limited de-identified data will be collected on eligible patients deemed as missed, including any imaging undertaken, and the presence or absence of CSI.

Case report forms (CRFs) will be used to collect relevant data at separate time points (figure 1).

**Figure 1 F1:**
[figure not shown]
Study flow. * Verbal consent for follow up required (CRF 3). CRF, case report form; ED, emergency department.

The clinician report form (CRF 1) will be completed by the treating clinician at the time of the ED visit. Data collected will include all possible predictor variables in the PECARN risk criteria^44^ and existing adult focused CDRs^32^,^35^ prior to management decisions. Additional information to be collected is detailed in table 4. Clinical management will proceed independent of study participation.

**Table 4 T4:** Data variables to be collected

Clinical report form (CRF)	Variables collected
Clinician report form (CRF 1)	All predictor variables for CDRs under consideration.Mechanism of injury, history of injury (including symptoms and signs prehospital) and clinical ED examination.Clinician perceived CSI likelihood, neck immobilisation practice, planned imaging.
Medical record review (CRF 2)	Detailed demographics; prehospital management; management and imaging undertaken elsewhere for this injury; time-related data (times of triage, clinician evaluation, ED and hospital discharge); duration of ED and hospital stay; admission status; specialty unit consultations; use, type and duration of spinal immobilisation; analgesia; observation duration; intensive care admission, need for intubation and ventilation, duration of ventilation and duration of intensive care unit admission; specialty unit follow-up; any neck injury related representations (and imaging and interventions arranged or completed at that time); all head and neck imaging and results; CSI-related and head-injury related surgical interventions; other significant injury and mortality.
Follow-up contact (CRF 3)	CSI related symptoms (including neck pain, limb weakness/sensory changes/paraesthesias); relevant health practitioner contacts; need for and duration of ED and hospital admissions (with review of the relevant medical record); use, type and duration of spinal precautions and neurological interventions; head and cervical spine imaging modalities and results; CSI-related and head injury-related surgical interventions.
Medical record review for patients with CSI at 12 months (CRF 4)	Imaging, interventions and outcomes at 12 months in patients with confirmed CSI.

CDRs, clinical decision rules; CSI, cervical spine injury; ED, emergency department.

A detailed medical record review (CRF 2) will be completed on or after 21 days after injury by the site research team, collecting information on patient demographics, management and outcomes (table 4).

Follow-up contact (CRF 3) by the site research team will be undertaken on patients who do not receive cervical spine imaging during their initial ED visit or on subsequent attendances (as identified by medical record review at 21 days). This follow-up is undertaken to minimise the potential for missed CSIs, as it is both unethical and unfeasible to image all children presenting with possible CSI due to concerns with exposure to ionising radiation, and healthcare resource use. Follow-up contact will occur 21–60 days after the injury via telephone or email (maximum of six attempts). If more than 60 days have elapsed, or there are six failed contact attempts, follow-up will be regarded as unsuccessful. The medical record for patients unable to be reached will be reviewed for injury-related attendances.

Patients with confirmed CSI who received ongoing follow-up at the hospital after the ED visit will have a retrospective review of the site medical record at twelve months to examine imaging, interventions and outcomes in this subgroup.

Verbal consent for follow-up contact will be obtained at the time of the initial ED visit or at parent/guardian contact during the 21–60 day follow-up period. A waiver of consent has been obtained for medical record review.

### Data management

Data for this study will be collected and entered using paper-based (CRF 1) and electronic data collection forms (CRFs 2–4) which will be completed by the treating clinician and research team, respectively. Participating clinicians (physicians and nurse practitioners) and the research team at all sites receive formal training prior to the commencement of the study. Standardised teaching materials have been created and provided to participating sites and a source document plan has been completed at each site to ensure data consistency.

All data will be de-identified and entered into a secure password-protected database enabled through the REDCap^51^ (Research electronic Data Capture) web-based application hosted by the Murdoch Children’s Research Institute, Melbourne, Australia. All data transmissions are encrypted. This database will only be accessible to trained research staff, with individual site research teams only having access to their own site’s data. Hard copy data will be stored in a secure location accessible only to the local research team. All sites will maintain a separate password-protected logbook, accessible only to local site staff on a secure online database containing reidentifying information for data queries and patient follow-up.

Recruitment, study process, data collection and data entry compliance will be regularly reviewed remotely and through in-person site visits as outlined in a study clinical monitoring plan. Monthly recruitment reports will be undertaken, and individual site support provided by the central coordinating team as required.

All data will be retained in line with ethics and governance requirements of the local site. An established study steering committee comprised of the central study team, local site principal investigators, spinal surgeons, statisticians and international experts will oversee study execution.

### Statistical methods

Statistical analyses will be performed once all data have been collected (with no plan for an interim analysis) using statistical software Stata IC 18.0^52^ or higher.

Demographic data and other relevant variables related to the management of CSI (eg, medical history, injury mechanism, mental status, physical examination) will be summarised as means and SD for continuous data (or medians and IQRs if skewed), or counts and percentages for categorical data, for all enrolled participants.

#### Accuracy analysis

All patients eligible for accuracy analysis will be used to externally assess performance accuracy (sensitivity, specificity, NPV and PPV) in identifying study-defined CSI, imaging-confirmed CSI and clinically important CSI of the PECARN risk criteria,^44^ and NEXUS^34^ and CCR^35^ CDRs. When applying each CDR, items will be scored as present, absent or unknown. ‘Unknown’ predictor variables will be imputed as ‘rule negative’. The estimates of each performance accuracy measure will be reported with exact binomial 95% CIs. A sensitivity analysis will be conducted for all accuracy outcomes by using available data only, treating unknown predictor variables as missing unless one of the completed predictor variables is already rule positive. An additional sensitivity analysis for all accuracy outcomes will include transferred patients who received cervical spine imaging with radiology reports at a non-participating centre. A subgroup analysis will be conducted that restricts the accuracy analysis for patients younger than 9 years and those 9 years and older.

The accuracy of each CDR will also be calculated using the exact inclusion, exclusions, predictor and outcome variables and definitions as set out in the original publications.^34 35 44^

#### Analysis of non-accuracy related outcomes

The entire data set that meets the definition of the study population (ie, those patients that meet all inclusion criteria and do not meet any exclusion criteria) will be used to analyse all other secondary outcomes not related to accuracy using only available data. The risk of study-defined, imaging-confirmed, clinically important CSI, CSI-related neurological abnormality and surgical intervention of the cervical spine, as well as methods of and adverse events associated with cervical spine immobilisation, will be estimated and reported with exact binomial 95% CIs. Duration of cervical spine immobilisation among those without injuries will be reported with median time and corresponding 95% CI. Determination of missed study-confirmed CSI rates with different cervical spine imaging modalities will be compared between each modality (XR, CT, MRI) by estimating a risk difference reported with a 95% CI and p value, using binomial regression. Bivariate associations between epidemiological factors (such as demographics, injury mechanism, medical history, mental status, physical examination) and cervical spine injury will be compared using a risk (binary outcome) or mean difference (continuous outcome) between those with and without cervical spine injury, estimated using either a binomial or linear regression model. For continuous outcome data that appear skewed (such as hospital length of stay), the data will be transformed on the log scale and groups will be compared using log-mean differences. All comparisons will also be reported with 95% CIs and p values.

There may be missing data in some secondary objectives that include the entire eligible sample (ie, non-accuracy related objectives). As such, we will conduct a sensitivity analysis where multiple imputation using chained equations will be used to handle the missing data under a plausible missingness assumption, if appropriate, when there is>5% missingness in key variables in the statistical model to assess the robustness of results.

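### Under an available-data rule, the median immobilisation time in uninjured children can lose imaged children whose collar came off outside the site record, which would bias it downward by an unknown, possibly small, amount

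*Protocol article*

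**What the plan says.** Duration of cervical spine immobilisation is part of a listed secondary outcome (Secondary outcomes). The section Analysis of non-accuracy related outcomes gives the summary: "Duration of cervical spine immobilisation among those without injuries will be reported with median time and corresponding 95% CI". The same section says that the full study population "will be used to analyse all other secondary outcomes not related to accuracy using only available data". A multiple-imputation sensitivity analysis is foreseen, if appropriate, "when there is>5% missingness in key variables in the statistical model to assess the robustness of results".

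The data sources are described in Table 4 and in the section on recruitment, study procedures and data collection:

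- **CRF 2, every child.** Table 4 lists "use, type and duration of spinal immobilisation", discharge times, and "specialty unit follow-up; any neck injury related representations". On timing: "A detailed medical record review (CRF 2) will be completed on or after 21 days after injury by the site research team".
- **CRF 3, follow-up contact.** It asks how long spinal precautions were used, but it "will be undertaken on patients who do not receive cervical spine imaging during their initial ED visit or on subsequent attendances".
- **CRF 4, 12-month review.** Confirmed CSI only, so it covers no uninjured child.

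**The concern.** For an imaged child without CSI, the site record is the only source of information after discharge. If the child goes home in a collar that is removed at another provider or by the family, and the site record never documents this, there is a start time and a documented minimum duration but no end time. An available-data median discards the minimum along with the child. Such children are likely to lie in the upper part of the distribution, so the loss is related to the value being measured and works in one direction.

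The article's Introduction gives discomfort and potential harm from spinal motion restriction as one reason why children should not be worked up needlessly. The median in uninjured children is the study's own measure of that burden, and understating it would make current practice look somewhat lighter than it is. The loss would also fall on imaged children only, since un-imaged children who are reached are asked directly.

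**Working it through.** The article states no figure for this outcome, so there is none to reproduce. The check has three parts.

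**1. Who can lack an end time**

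| Child | CRF 2 (day 21 or later) | CRF 3 | CRF 4 |
|---|---|---|---|
| Not imaged, no CSI | yes | yes, if reached | no |
| Imaged, no CSI | yes | no | no |
| Confirmed CSI | yes | only if not imaged | yes, if followed up at the hospital |

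The exposed group is the second row, and within it only children whose collar removal does not appear in the site record.

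**2. Effect on the median**

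Let m be the share of immobilised uninjured children with no recorded end time, and assume that all their true durations exceed the true median. The available-data median then sits at the 50(1 − m)th percentile of all children, and the true median is the 0.5/(1 − m) quantile of the observed times. If observed times are log-normal with log-SD s, then true/reported median = exp(s × z(0.5/(1 − m))). The article gives neither m nor s. Assumed ranges: m from 1% to 20%, s from 0.5 to 1.2.

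Example, m = 10%, s = 0.8: 0.5/0.9 = 0.5556, z = 0.140, exp(0.8 × 0.140) = 1.118.

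| m | Percentile reported as the median | True/reported, s = 0.5 | s = 0.8 | s = 1.2 |
|---|---|---|---|---|
| 1% | 49.5 | 1.006 | 1.010 | 1.015 |
| 2% | 49 | 1.013 | 1.021 | 1.031 |
| 5% | 47.5 | 1.034 | 1.054 | 1.082 |
| 10% | 45 | 1.072 | 1.118 | 1.183 |
| 20% | 40 | 1.173 | 1.290 | 1.466 |

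On an illustrative reported median of 3 h (180 min), the shift is 1 to 3 min at m = 1%, 6 to 15 min at 5%, and 31 to 84 min at 20%.

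**3. Whether censoring repairs it**

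A simulation of 20,000 children used in-hospital times that were log-normal with median 3 h and log-SD 0.8. A share went home in a collar for 5 to 21 further days. Children without a recorded end were censored 2 h after their drawn in-hospital time. Medians in hours:

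| Home in collar | End times lost | True | Available data | Kaplan-Meier |
|---|---|---|---|---|
| 2% | all | 3.07 | 3.00 | 3.07 |
| 5% | all | 3.13 | 2.97 | 3.13 |
| 10% | all | 3.35 | 3.00 | 3.34 |
| 20% | all | 3.88 | 3.00 | 3.82 |
| 2% | half | 3.06 | 3.03 | 3.06 |
| 5% | half | 3.14 | 3.05 | 3.14 |
| 10% | half | 3.33 | 3.15 | 3.32 |
| 20% | half | 3.87 | 3.41 | 3.83 |

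Kaplan-Meier removes nearly all of the bias. The remainder at 20% (3.82 against 3.88) arises because children who go home in a collar stay in it longer than those still at risk in hospital, so the censoring is informative. Ranking the censored children above the median avoids that assumption: at m = 20% and s = 0.8 it gives 3 × 1.290 = 3.87 h.

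**The case against.** The strongest reply is that the article nowhere says such children will be lost.

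- **CRF 2 is not cut off at discharge.** It is completed at day 21 or later and captures duration, specialty follow-up and re-presentations for every child. Table 3 defines one form of clinically important CSI by immobilisation beyond 7 days, so the study evidently expects to recover durations of that length in injured children. This stands. A reader might infer that every imaged child who leaves in a collar has no end time. The documents do not support that: only removals absent from the site record are affected.
- **The estimator is open.** A median time with a confidence interval is compatible with Kaplan-Meier, and a censored time can be called available data. The analysis plan, which is not shown, may say so. This stands in part. Censoring is not excluded, but it is not mentioned either, and the plain reading of the stated rule is to omit a child without a duration.
- **Medians resist loss in the tail.** This stands for small losses. A reader might infer that the reported median will definitely be too short by a material amount. With no share in the document, that cannot be claimed.
- **Multiple imputation is planned.** It is only a partial answer. It is a sensitivity analysis, conditional on more than 5% missingness and on being appropriate, and the text does not say that it would use the known minimum duration. It would equally be wrong to assert that it must fail, because the article commits only to a plausible missingness assumption.

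**Conclusion.** The point holds in a conditional form. Collection after discharge is unequal between imaged and un-imaged uninjured children, and the available-data rule, taken literally, drops any imaged child whose end time is missing from the site record. If those durations exceed the median, as is likely for a collar worn home, the bias is downward.

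Its size is unknown. Under log-normal times with log-SD 0.5 to 1.2, the true median would be about 1 to 3% longer than reported if 1 to 2% of children are affected, 3 to 8% at 5%, and 7 to 18% at 10%. The shift thus reaches about 10% only when roughly a tenth of the children lack an end time. If the record supplies half of the end times, the shortfall is roughly halved.

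The outcome is a descriptive summary and does not feed the accuracy estimates, so this is an inexpensive improvement rather than a threat to the study.

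**What to change.** State in the analysis plan, for this outcome:

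1. Every immobilised uninjured child is kept in the analysis.
2. A child with no recorded end is right-censored at the last record that documents immobilisation, or at discharge if nothing later exists. Always censoring at discharge would discard follow-up that the day-21 review may have found.
3. The Kaplan-Meier median is reported with its 95% CI.
4. Because the censoring may be informative, a bound is added in which these children rank above the median. It needs no end times.
5. The proportion with no recorded end time is reported, preferably split by imaged and un-imaged. If it is 1 to 2%, the issue is shown to be negligible.

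Cost: slightly more analysis work, using duration and discharge times already listed for CRF 2. No new data collection is needed and clinical care is unaffected. The reported median may become slightly longer.

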#### Sample size

The sample size has been calculated based on a secondary outcome (derivation and validation of a new exploratory SONIC CDR), as the sample size required for this will be higher than for the primary outcome. Although not based on the primary outcome, given we expect more events based on this sample size than if the study were powered on the primary outcome, we consequently expect considerable certainty in the estimates of the performance accuracy measures. Based on the prospective pilot study of~1000 children with suspected CSI with~0.5% CSI,^45^ we expect to be able to enrol up to 30 000 patients at 14 sites over 3 years. A high enrolment rate and low loss to follow-up rate is expected based on experience in a similar study.^47^

We will continuously grow the cohort and use all the patients enrolled at the time that 100 CSIs have been identified to derive the rule, and the additional cohort when an extra 50 CSIs have been enrolled to validate the resulting rule. If the rate of CSI is higher than expected, we will be able to reduce the total number of enrolled patients for derivation and validation cohorts. A retrospective pilot study at one of the study hospitals^53^ (CSI rate of 4%) indicated that the expected CSI rate may be higher, which would either increase the precision of the results or reduce the required total number of enrolled patients. The total patient number needed will therefore be adjusted as the study progresses. The CSI rate among enrolled participants to date is higher than the assumptions used to calculate the sample size.

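### With about 150 CSI children against thousands without, continuous comparisons should name a robust or unequal-variance standard error (optional, cost-free improvement)

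*Protocol article*

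**What the plan says.** In the protocol article, under Analysis of non-accuracy related outcomes, associations between epidemiological factors and CSI are summarised for continuous variables as a "mean difference (continuous outcome) between those with and without cervical spine injury, estimated using either a binomial or linear regression model". Skewness has its own remedy: "For continuous outcome data that appear skewed (such as hospital length of stay), the data will be transformed on the log scale", and log-means are then compared. On inference: "All comparisons will also be reported with 95% CIs and p values". The text does not say whether standard errors are model-based or robust, and it gives no SD for any continuous variable in either group.

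Group sizes come from the Sample size section. The plan is to "use all the patients enrolled at the time that 100 CSIs have been identified to derive the rule", and then to use "the additional cohort when an extra 50 CSIs have been enrolled to validate the resulting rule". The planning rate is about 0.5% CSI with enrolment of up to 30,000. The section also cites a retrospective pilot with a 4% rate and reports that the rate so far is above the planning assumption, without giving the figure.

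**The concern.** The question is whether the mean (or log-mean) differs between children with and without CSI. Linear regression on a group indicator, with its default standard error, answers it under the added assumption that both groups have the same residual SD. With groups of similar size, a breach of that assumption does little harm. Here the groups are extremely unequal by design. The pooled SD is set by the large non-CSI group, while the uncertainty of the difference comes almost entirely from the small CSI group, so the default model takes its error bars from the wrong group.

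If CSI children are the more variable group, the intervals are too narrow and p values too small. If they are less variable, the intervals are too wide and power is lost. The log transform is aimed at skewness. It may bring the spreads closer, but it does not make them equal. These comparisons feed the epidemiology of CSI, a listed secondary outcome that the Discussion presents as one of the study's contributions.

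**Working it through.** **Inputs from the article (Sample size section).** CSI events: 100 + 50 = 150. Planning CSI rate: 0.5%. Alternative rate: 4%.

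**Assumptions.** Two-sided nominal 5%. SD ratio r = SD in CSI children / SD in non-CSI children, shown over a range because the article gives none. The non-CSI SD is set to 1 without loss of generality.

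**Step 1. Reproduce the plan's enrolment figure.** 150 / 0.005 = 30,000, which matches the stated maximum. Non-CSI children: 30,000 − 150 = 29,850. At 4%: 150 / 0.04 = 3,750, so 3,600 without CSI.

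**Step 2. Where each standard error gets its information.** The non-CSI group's weight in the pooled variance is (n0 − 1)/(n1 + n0 − 2). This is 29,849/29,998 = 99.5% at the 0.5% rate and 3,599/3,748 = 96.0% at 4%. The CSI group's share of the true variance of the difference, at equal SDs, is (1/n1)/(1/n1 + 1/n0), which is again 99.5% and 96.0%. The two standard errors therefore lean on opposite groups.

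**Step 3. Model-based against true standard error.**

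- Model SE = s_p × √(1/n1 + 1/n0), with s_p² = [(n1 − 1)r² + (n0 − 1)]/(n1 + n0 − 2)
- True SE = √(r²/n1 + 1/n0)
- Actual type I error = 2 × [1 − Φ(1.96 × model SE / true SE)]

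Worked case, r = 2, 150 v 29,850: s_p² = (149 × 4 + 29,849)/29,998 = 1.0149. Model SE = √(1.0149 × 0.0067002) = 0.0825. True SE = √(4/150 + 1/29,850) = 0.1634. Their ratio is 0.505, and 1.96 × 0.505 = 0.99, so the type I error is about 32%.

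| r | SE ratio, 150 v 29,850 | Type I error (CI coverage) | SE ratio, 150 v 3,600 | Type I error (CI coverage) |
|---|---|---|---|---|
| 0.8 | 1.247 | 1.5% (98.6%) | 1.227 | 1.6% (98.4%) |
| 1.0 | 1.000 | 5.0% (95.0%) | 1.000 | 5.0% (95.0%) |
| 1.1 | 0.910 | 7.5% (92.6%) | 0.916 | 7.3% (92.7%) |
| 1.5 | 0.670 | 18.9% (81.1%) | 0.691 | 17.6% (82.4%) |
| 2.0 | 0.505 | 32.3% (67.7%) | 0.537 | 29.3% (70.8%) |

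**Step 4. Check by simulation.** With 4,000 replicates of normal data per setting, the pooled test at 150 v 29,850 rejected in 1.3%, 4.6%, 7.8%, 19.3% and 32.9% of replicates at r = 0.8, 1, 1.1, 1.5 and 2, in agreement with the formula. The unequal-variance (Welch) test stayed at about 4.5% to 5.6% in every setting at both group sizes.

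**Step 5. Cost if the spreads are equal.** At r = 1 and 150 v 29,850, the Welch degrees of freedom are (1/150 + 1/29,850)² / [(1/150)²/149 + (1/29,850)²/29,849] ≈ 150. The critical value is 1.976 instead of 1.960, so the interval is about 0.8% wider (1.976/1.960 = 1.008).

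**The case against.** The strongest objection is that the article never commits to an equal-variance model. It names linear regression, which is fully compatible with robust standard errors and gives the same mean difference either way. The choice of variance estimator is a detail often left to a full protocol or SAP, and neither is shown. This stands: a reader might infer that the plan specifies ordinary least squares with pooled errors, and the text does not support that. It supports only the conditional statement that the default would be miscalibrated if it were used and the spreads differed.

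Three further limits also stand.

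- **Unequal spread is not shown.** A reader might take the article's own example, length of stay, as evidently more variable in CSI children. But eligibility also admits children with severe other injuries and no CSI, so neither the direction nor the size of any difference can be read from the document. For age, bounded below 16 years, the SD cannot exceed 8. If non-CSI ages were roughly uniform (an assumption; SD 16/√12 = 4.6), the ratio could not exceed 8/4.6 ≈ 1.7.
- **The scope is narrow.** Many of the listed factors are categorical and would be compared by risk differences. The comparisons are descriptive, and the section attaches no decision rule to their p values.
- **The 29,850 is an upper bound.** The CSI rate so far exceeds 0.5%. This does not rescue the default, however: at 4% the error is still 17.6% at a ratio of 1.5.

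What the objection does not remove is that the article fixes the estimand, the model, the remedy for skewness and the form of inference, and that the imbalance making the variance estimator matter is built into the design.

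**Conclusion.** The point holds conditionally, as an optional improvement and not as a demonstrated error. If default model-based standard errors are used and the SDs differ, a nominal 5% test has an actual error of about 7% at an SD ratio of 1.1, 18–19% at 1.5 and 29–32% at 2, and about 1.5% at 0.8. The ranges span the 4% and 0.5% CSI rates with 150 CSI children. The ratios are assumptions; at a ratio of 1 there is no problem, and near 1 the effect is small.

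A reader might go further and conclude that the study's published intervals will be wrong, or that its main results are at risk. The document supports neither. An SAP may already specify robust errors, and the primary accuracy measures use exact binomial intervals, which this point does not touch. Only secondary, descriptive comparisons of continuous variables are affected.

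**What to change.** In Analysis of non-accuracy related outcomes, or in the SAP if it is not already there, add one phrase: mean and log-mean differences between children with and without CSI will be estimated by linear regression with heteroscedasticity-robust standard errors (for example HC3, available in Stata as vce(hc3)) or reported with the equivalent Welch interval.

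The cost is that phrase and one software option. No further data or patients are needed, and the point estimates do not change. Because the analyses run only after all data are collected, with no interim analysis planned, the choice can still be fixed in advance.
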